### Data handling

Investigators will enter the collected data required by the protocol into the case report forms. Non-obvious errors or omissions will be recorded on data query forms, which will be returned to the researchers’ workshop for resolution. The data from all centers will be pooled and summarized with respect to demographic baseline characteristics, effectiveness and safety observations.

### Patient safety

Any adverse experiences (known as unfavorable or unintended signs, or symptoms or disease occurring after treatment) related to EA treatment will be monitored. The research team will review all trial protocols, monitor subject safety, and investigate any adverse events. Trials will be terminated if there are concerns for patient safety.

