**Figure 1 F1:**
[figure not shown]
Flow chart of study process.

**Table 1 T1:** Timing of visits and data collection

	**Week - 1**	**Week 0**	**Week 2**	**Week 4**	**1 month**	**3 months**
	**Baseline**	**Treatment phase**			**Follow-up phase (end-of-treatment)**	
Patients						
Informed consent	**×**					
Sign the informed consent		**×**				
Medical history	**×**					
Physical examination	**×**					
Randomization		**×**				
Intervention						
Electroacupuncture group (n = 18)		20 sessions of EA at *Jing-jiaji* points				
Comparisons						
Acupuncture group (n = 18)		20 sessions of acupuncture at *Jing-jiaji* points				
Outcomes^a^						
NPQ		**×**	**×**	**×**	**×**	**×**
MPQ		**×**	**×**	**×**	**×**	**×**
SF-36		**×**	**×**	**×**	**×**	**×**
Participants safety						
Adverse events		**×**	**×**	**×**	**×**	**×**

^**a**^NPQ, Northwick Park Neck Pain Questionnaire; MPQ, McGill Pain Questionnaire; SF-36, Short-Form 36 Scale.

This trial will include a four-week treatment period and a three-month follow-up period. After randomization, patients will receive 20-session treatments over a period of four weeks. Outcome measurements will be assessed at baseline (that is, one week after subjects are diagnosed with CS), as well as at the end of the second week and four weeks after randomization, and one and three months after conclusion of the treatment phase respectively. Patients will be informed that they may be assigned to an EA group, or an acupuncture group.

This trial will be carried out according to the principles of the Declaration of Helsinki (version Seoul 2008). This study protocol has been approved by the ethics review boards of the Second Affiliated Hospital of Heilongjiang University of Traditional Chinese Medicine, with permission number LLP2012029. All participants will be asked to provide written informed consent before enrollment having been given adequate time to consider what the trial involves. For subjects who decline to agree to participate in EA, other treatment options will be available.

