### Randomization and allocation concealment

A randomization scheme will be conducted by the Evidence-Based Medicine Center of the Second Affiliated Hospital of Heilongjiang University of Traditional Chinese Medicine. According to a random sequence table, generated by SAS 8.2 software (SAS software (Beijing) Co., Ltd, [name]), participants who meet the inclusion criteria will be allocated randomly into an EA group and an acupuncture group in a 1:1 ratio. Two separate databases will be set up. One (participants’ database) includes basic information on issues such as name, contact details and so on, while the other (randomization database) holds data on patients registered in the trial and their allocation
[25]. The randomization sequence schedule of group assignments and detailed treatments will be prepared by the Evidence-Based Medicine Center of the Second Affiliated Hospital of Heilongjiang University of Traditional Chinese Medicine and sealed in opaque envelopes. These sealed envelopes will be marked with the patients’ sequential numbers and kept by the screeners, who are not involved in the study.

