### Intervention

Intervention was designed according to record in the ancient book of *Yellow Emperor’s Inner Bible*[28] and according to recent studies of acupuncture as a treatment for CS. Subjects will receive acupuncture at bilateral acupuncture points *Jing-jiaji* (EX-B2.C4), *Jing-jiaji* (EX-B2.C5), and *Jing-jiaji* (EX-B2.C6). Sterile disposable acupuncture needles (40 mm in length and 0.30 mm in diameter; Andy brand, Guizhou Andy Medical Instrument Co., Ltd. (
http://www.andiyx.com; [contact]) will be perpendicularly inserted to a depth of 20 to 30 mm above the *Jing-jiaji* points in both groups. EA protocol was developed in consensus with acupuncturists and experts, who are good at acupuncture. In addition, this protocol is consistent with the STRICTA guidelines for the performance of EA studies
[29].

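### The safety section limits monitored adverse experiences to those attributed to electroacupuncture, which conflicts with its own next sentence and with Table 1 and could lead to unequal recording in the two arms

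*Protocol article*

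**What the plan says.** Four places in the protocol article bear on which adverse events are recorded.

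- **Patient safety, first sentence:** "Any adverse experiences (known as unfavorable or unintended signs, or symptoms or disease occurring after treatment) related to EA treatment will be monitored". This is the only sentence that says which experiences are monitored, and it limits them to those attributed to EA.
- **Patient safety, second sentence:** the research team will "monitor subject safety, and investigate any adverse events". There is no limit by arm or by cause.
- **Design, Table 1** ("Timing of visits and data collection"): under the heading "Participants safety" an adverse-event row is marked at week 0, week 2, week 4, 1 month and 3 months. The table lists both arms, with n = 18 each, and the row is not confined to either.
- **Data handling:** "The data from all centers will be pooled and summarized with respect to demographic baseline characteristics, effectiveness and safety observations". Safety is named without restriction.

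Three further sections give the setting. Participants are "allocated randomly into an EA group and an acupuncture group in a 1:1 ratio". Under Intervention, needles are inserted "to a depth of 20 to 30 mm above the *Jing-jiaji* points in both groups". Under Treatment group, the EA arm has the electrical apparatus connected in addition to the needling.

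**The concern.** The arms differ by the electrical stimulation. The safety question this design can answer is therefore whether stimulation adds risk over needling alone, and that requires adverse events to be collected by the same rule in both arms.

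The first safety sentence does not give such a rule. An event in a patient who never received EA cannot be related to EA, so on the literal wording no acupuncture-arm event qualifies. In the EA arm an event qualifies only if someone attributes it to EA. The Blinding section says that acupuncturists and patients cannot be blinded, so that attribution is open to knowledge of the allocation.

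An analysis plan could not repair this later, because an event that was never recorded cannot be recovered at analysis. The trial is also described as a pilot for a larger study, so a distorted safety picture could carry forward.

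**Working it through.** No figure is involved, so the check is a comparison of passages.

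**Step 1: who can satisfy the narrow sentence.**

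| Arm | Planned n | Needled | Receives EA | Can an event be attributed to EA? |
|---|---|---|---|---|
| Electroacupuncture | 18 | Yes, 20 sessions | Yes | Yes, if judged so |
| Acupuncture | 18 | Yes, 20 sessions | No | No |

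On the literal reading, 18 of 36 participants, or 18/36 = 50%, cannot contribute a qualifying event. Because both arms are needled on the same schedule, events caused by needling can occur in either.

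**Step 2: the four statements on scope, side by side.**

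| Place | Limited by arm? | Limited by cause? |
|---|---|---|
| Patient safety, first sentence | In effect, yes | Yes, to EA |
| Patient safety, second sentence | No | No |
| Table 1, adverse-event row | No | No |
| Data handling | No | No |

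One statement is narrow and three are not.

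**Step 3: do the broader statements settle the matter?** Not fully. Table 1 fixes when adverse events are recorded and shows that the schedule covers both arms, but it does not define which events count. The second safety sentence describes what the team does about events, and need not be read as a rule for collection. Data handling describes summarising what was entered, and says that investigators enter what the protocol requires. The only sentence that characterises the required events is the narrow one. A member of staff could follow either reading in good faith, and the article does not say which prevails.

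**Step 4: the timing words.** The bracketed definition places events after treatment. That may mean after treatment has begun, and the marks in Table 1 at weeks 0, 2 and 4, inside the treatment phase, fit that sense. No weight is placed on these words.

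**Step 5: consequence.** If the narrow sentence is followed, or is followed by some staff and not others, ascertainment can differ between arms. The direction of the resulting bias is not determined. Leaving out acupuncture-arm events would make EA look worse, while strict attribution in the EA arm would reduce its own count.

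**The case against.** The strongest reply is that one loose sentence is outweighed by the rest of the article. The data-collection schedule covers both arms at five time points, the very next sentence is unrestricted, and Data handling promises a safety summary. Nothing ranks the narrow sentence above these.

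Much of this stands. A reader might infer that acupuncture-arm events and unattributed events will not be captured and that the arms cannot be compared for safety. The documents do not support that: Table 1 and the second safety sentence both point the other way. A reader might also infer that events during the treatment course are excluded, but the wording on timing is ambiguous and the schedule suggests they are included. Nor does the article say that unblinded staff must judge relatedness before an event is recorded. It does not name who makes that judgement or when, and outcome assessors are to be blinded. The exposure to unblinded attribution is a risk that the wording leaves open, not a stated procedure.

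It may also be said that a journal article leaves safety detail to the full protocol and case report form. That is fair for detail, but the point here is not an omission. The article states a scope, and that scope conflicts with its other statements.

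**Conclusion.** The point holds as an internal inconsistency with a possible consequence for the safety comparison. The first sentence of Patient safety is narrower than the sentence after it and than Table 1. If applied as written, it would exclude events in the acupuncture arm and make capture in the EA arm depend on attribution.

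The reach of the literal reading is half of the planned sample. The size of any bias cannot be stated, because the documents give no adverse-event rate and do not show how staff will resolve the conflict. The conclusion assumes only that some staff may treat the narrow sentence as the recording rule; if all follow Table 1 without restriction, no harm results. The efficacy outcomes (NPQ, MPQ and SF-36) are unaffected. Since the Trial status section says recruitment is under way, the wording should be settled promptly.

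**What to change.** Reconcile the passages by removing the EA restriction from the first sentence of Patient safety. Suggested replacement: all adverse events in both groups, from the first session to the 3-month visit, will be recorded at the visits shown in Table 1, whatever their relation to treatment; relatedness to the assigned treatment will be classified separately afterwards; events will be summarised by group.

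Check that the case report form carries the same scope, so that staff do not apply the narrower wording. The visits are already scheduled, so the cost is a rewritten sentence, a form check and slightly more data entry.

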### Quality control

All staff are required to undergo special training, including patient selection and exclusion, filling-up of the case report and acupuncture method, before participating in the trial. The monitors will check on case reports, and EA operation at the participating hospital twice a month. Drop-outs, withdrawals (and the reasons) from the study will be fully documented throughout the treatment and follow-up periods.

### Ethics

This trial is approved by the ethics review boards of the Second Affiliated Hospital of Heilongjiang University of Traditional Chinese Medicine.

## Discussion

CS neck pain remains a major public health problem. The results of this study will focus on neck pain caused by CS and will determine if EA is an effective intervention for this kind of symptom relief.

Acupuncture, one of the most important parts of traditional Chinese medicine, has been a form of health care in China for thousand years. It has been reported to have some benefits to CS patients, and also enhance their signs and symptoms.

Currently, no studies about EA treatment at *Jing-jiaji* points for patients with CS neck pain have been published; therefore, we designed this trial. This study aims to conduct a pilot study for a full scale trial of electroacupuncture at *Jing-jiaji* points for CS neck pain, and to look at its potential effectiveness in terms of CS neck pain of future episodes. Moreover, it also provides the feasibility of a large clinical trial. The data pooled will shed new light on acupuncture, especially for EA therapy for CS neck pain.

## Trial status

The trial is currently recruiting subjects.

## Abbreviations

ChiCTR: Chinese clinical trials register; CS: Cervical spondylosis; EA: Electroacupuncture; ITT: Intention-to-treat; MPQ: McGill pain questionnaire; NPQ: Northwick Park neck pain questionnaire; NSAID: Non-steroidal antiinflammtory; SF-36: Short-Form 36 scale.
